### Study Materials

#### Articles (Learning Content)

Two published medical articles have been selected to represent different levels of complexity within the field of cardiology, both published in *BMC Cardiovascular Disorders*.

The *narrative* article is a case-based clinical report [22]. This report describes the diagnostic journey and clinical management of a patient with eosinophilic myocarditis who presented with cardiogenic shock and malignant arrhythmias. The article is structured in a narrative format and emphasizes clinical reasoning, interdisciplinary care, and escalation of treatment. It presents practical, concrete decision-making steps, making it highly accessible and relevant for clinical-phase medical students.

The *technical* article focuses on the validation of 3-dimensional echocardiographic measurements of the vena contracta area for quantifying mitral regurgitation severity [23]. It involves advanced imaging techniques, direct planimetry, multiplanar reconstruction, and statistical comparisons, including sensitivity and specificity analysis and Bland-Altman plots. The dense methodological content and reliance on imaging expertise and statistical interpretation make it cognitively demanding and better suited for advanced learners with prior knowledge of cardiac imaging and valvular pathology.

These articles were deliberately chosen to provide a clear contrast in complexity and content delivery within the same specialty and text length (8 pages), allowing for an effective assessment of learning outcomes across different formats and difficulty levels.

For the reading groups, the article text will be provided on a screen in PDF format. For the podcast groups, the content of these articles is used as input to generate the AI podcasts.

#### AI-Generated Podcasts

Using Google NotebookLM (an AI platform currently in experimental release) [24,25], we generated an audio summary for each of the 2 articles. The process involves uploading the article text into NotebookLM and then using the “audio overview” feature. The output is an audio file featuring 2 synthetic voices (the *AI hosts*) discussing the article. According to NotebookLM’s design, the hosts begin by introducing the topic, then proceed to discuss key points, clarify terms, and make connections. This is similar to one host quizzing or interviewing the other about the article’s content. The tone is meant to be conversational, which can help maintain listener interest.

Google NotebookLM was chosen for this study because, at the time of design, it was the only publicly accessible platform capable of generating conversational, dialogue-style audio summaries directly from full-text academic articles with no need for additional scripting. Its *audio overview* feature automatically organizes content into a simulated exchange between 2 hosts. This format aligns with well-established educational strategies, such as elaborative interrogation and peer explanation, which can foster learner engagement and retention. While alternative AI tools can produce summaries, they typically provide plain-text outputs or monologue-style narrations and require substantial manual adaptation to achieve a similar conversational format. Using NotebookLM enabled us to create standardized, pedagogically relevant podcasts with minimal human editing, thereby reducing the risk of inadvertent bias in the intervention materials while maintaining ecological validity for real-world use cases.

Each resulting podcast is approximately 15 minutes in length. The audio files are in English, matching the article's language. We reviewed the transcripts of these AI-generated discussions to ensure they cover the main sections of the articles (eg, the case presentation and outcome in the narrative article, and all major subtopics in the technical article). We also checked for any factual inaccuracies or misrepresentations.

During the session, participants in the podcast conditions will listen to the audio using over-ear headphones provided by the study team (to ensure good sound quality and noise isolation). The audio will be played on a tablet or computer via a simple media player interface. Participants will be instructed that they can pause, rewind, or replay the audio as needed (up to 1 full listening of the entire length again, if time allows), but they cannot fast-forward beyond sections they have not heard yet (to prevent skipping content). They will not have a transcript or any text of the article while listening to simulate a true audio-only learning experience.

#### English Proficiency

Participants will rate their level of English proficiency along the dimensions of *listening*, *reading*, *participating in conversations*, and *coherent speech* [26]. For each dimension, they will be given 6 levels (from A1 to C2) with short descriptions, such as “I can understand individual words and parts of sentences” (listening A1) or “I can write clear, fluent, stylistically appropriate reports, articles, and sophisticated letters” (coherent speech C2). English proficiency will be considered sufficient if no dimension is reported to be below B2.

#### Knowledge Tests

For each article, we developed a multiple-choice questionnaire to assess the comprehension and retention of key information. Each test consists of 10 questions in a single-best-answer format, and the sum of all correct answers represents the knowledge score. The questions cover important points from the article.

All questions were written specifically for this study. We ensured that each question could be answered based on the information in the article and that the AI podcast, if accurate, would also cover those points. We had 2 faculty members with a background in cardiology who were not involved in the study review the questions for content validity and clarity. Internal testing of the final items yielded no problems with comprehensibility.

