Producing high-quality medical education podcasts typically requires expert knowledge, pedagogical insight, technical skills, and significant time for scripting, recording, and postproduction [18]. These constraints limit scalability and personalization, especially for institutions or learners aiming to integrate podcasts into dynamic, content-rich environments, such as medical curricula. Recent advances in generative artificial intelligence (AI) present an opportunity to overcome some of these barriers. AI-powered systems based on large language models can now generate podcast-style summaries of academic content by transforming articles into structured, conversational dialogues [16]. These AI-generated podcasts often simulate discussions between 2 virtual hosts, aiming to translate complex material into an engaging audio narrative. Early research indicates that such podcasts can enhance learner motivation and satisfaction, particularly when personalized according to user needs [19]. Some studies suggest comparable or even superior learning outcomes relative to traditional reading in specific contexts [17,19].

Nevertheless, the educational value of these AI-generated summaries remains largely untested in medical education [18]. AI-generated podcasts may lack the necessary accuracy or lose important contexts, which may cause either worse learning outcomes or potentially even misinform learners and endanger patients. Therefore, this study aims to address these questions through a randomized controlled trial comparing learning outcomes across 2 types of medical articles (practical vs theoretical) in the reading and listening modalities. By examining both knowledge acquisition and learners’ motivational and cognitive responses, we aim to assess whether AI-generated podcasts can serve as a viable tool for engaging residents with scientific literature.

The primary objective of this randomized trial is to compare knowledge acquisition from medical journal articles between 2 learning modalities: listening to an AI-generated podcast versus reading the full text. We seek to determine if one modality leads to superior comprehension in medical residents. A secondary objective is to assess the influence of article complexity on learning outcomes and any interaction between complexity and modality.

In operational terms, the study will test two main hypotheses and one interaction hypothesis, as presented in Textbox 1.

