**Modality × complexity interaction**
We hypothesize an interaction such that the effectiveness of the podcast relative to reading will differ by article complexity. Specifically, the performance gap (if any) between listening and reading is expected to be larger for the complex article than for the easy article. In other words, for the easier, case-based article, listening to a summary might achieve nearly the same comprehension as reading, whereas for the complex article, listening to the summary might not capture enough detail, leading to lower comprehension compared to reading the full text.

Additional objectives include evaluating secondary outcomes related to the learning experience: we will compare residents’ intrinsic motivation during the task, subjective cognitive load, and their subjective perception of learning between the 2 modalities. This will provide a more nuanced understanding of how engaging or difficult residents found the learning process in each condition, beyond the factual knowledge gains. Ultimately, the goal is not only to determine which method yields higher test scores, but also to consider which method residents prefer or find more motivating, because an engaging learning experience could encourage more frequent interaction with the scientific literature.

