## Discussion

### Anticipated Findings

This study evaluates AI-generated audio summaries (*AI podcasts*) as a tool for learning from scientific literature in postgraduate medical education. By directly comparing podcast-based learning with the traditional method of reading full-text articles, we aim to generate evidence on comprehension outcomes, learner motivation, cognitive load, and perceived learning. Because each participant will experience both modalities—reading and listening—our within-subjects design allows for more precise comparisons while controlling for individual differences in prior knowledge, attention, and learning preferences.

The findings will have practical implications for adapting learning materials for resident physicians preparing for board certification. If we find that reading leads to significantly better comprehension than listening, particularly for complex or technical content, this suggests that caution is warranted in using audio summaries as a standalone resource. Resident physicians may miss subtle but clinically important nuances when relying solely on AI-generated podcasts for learning. In such a case, AI-generated audio could still be valuable as a supplementary tool—useful for introducing new material, reinforcing key ideas, or supporting review during time-constrained situations such as commuting or night shifts. The results could also inform developers and content curators about the limitations of current AI summarization models, especially for dense scientific material, and point to areas where greater fidelity and detail are needed.

On the other hand, if comprehension is equivalent across modalities, even for technical articles, this would support the integration of AI-generated audio into formal and informal learning routines. AI podcasts could then be leveraged to increase the flexibility with which physicians access and absorb scientific information, without compromising accuracy or depth. Medical educators and institutions might consider systematically producing and offering AI-generated audio summaries of core readings or recent guideline updates, especially for busy clinicians with limited time for traditional study methods.

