### Limitations

We acknowledge several limitations of our study. First, our findings will be specific to the 2 articles chosen. While we intentionally selected examples of narrative and technical articles, they are only single instances of those categories. Thus, generalizing to all *narrative vs technical* content should be done cautiously. The results might differ with other topics or types of papers. Ideally, a follow-up study with more varied content would strengthen generalizability. Moreover, the expert screening of AI-generated podcasts may be influenced by confirmation bias during transcript editing, suggesting the need for additional studies replicating our findings based on different podcast outputs. Moreover, article identity is confounded with complexity, as only 1 narrative and 1 technical paper were used. This limits external validity and precludes treating article as a random factor. Future studies should include multiple articles per complexity level to strengthen generalizability and allow for modeling article-level variance.

Furthermore, our design does not fully disentangle the effects of learning modality (listening vs reading) from those of content completeness (summary vs full text). The AI-generated podcasts used in this study provide condensed, dialogue-style overviews and do not provide access to the original figures or data tables. In contrast, the reading condition involves the complete article. Consequently, any differences in comprehension could reflect the presentation modality and informational scope. We intentionally opted for this naturalistic comparison because AI-generated summaries are likely to be used as practical alternatives to reading full articles in real-world contexts. Nevertheless, future research should seek to match content more closely across modalities, for instance, by comparing narrated full-text versions with written full texts, or written summaries with audio summaries, and ensuring equitable access to visuals. Such studies would help clarify whether comprehension differences stem primarily from modality or from differences in content coverage and depth.

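### Knowledge-test items are confined to points an accurate podcast would cover, so the primary endpoint is largely insensitive to omitted content and does not support the planned conclusions on depth or missed nuance

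*Protocol article*

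**What the plan says.** **The instrument.** Knowledge Tests describes one test per article: "Each test consists of 10 questions in a single-best-answer format". The score is the number correct, and the stated purpose is "to assess the comprehension and retention of key information". The item rule is that "each question could be answered based on the information in the article and that the AI podcast, if accurate, would also cover those points". Two cardiology faculty members outside the study reviewed the items, and internal testing found no problem with comprehensibility.

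**The podcasts.** The section AI-Generated Podcasts reports: "We reviewed the transcripts of these AI-generated discussions to ensure they cover the main sections of the articles". It adds a check for factual errors. It does not say that the test items were compared with the transcripts.

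**The expectation.** The Introduction warns that "AI-generated podcasts may lack the necessary accuracy or lose important contexts". In Textbox 1, the modality hypothesis expects any benefit of reading to lie chiefly in detailed content. The interaction hypothesis says that, for the complex article, "listening to the summary might not capture enough detail, leading to lower comprehension compared to reading the full text".

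**The planned reading.** Under Anticipated Findings, equal comprehension, even for the technical article, would support wider use of AI audio "without compromising accuracy or depth". Better scores after reading would be taken to mean that residents who rely on podcasts may overlook fine but clinically relevant points. Limitations adds that "any differences in comprehension could reflect the presentation modality and informational scope", and does not mention the item rule.

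**The concern.** The hypothesis and the instrument point in different directions. The trial expects the podcast to do worse partly because a summary leaves things out, and expects this most for the technical article. The item rule then keeps off the test what an accurate summary leaves out. Such content can neither earn a reader a point nor cost a listener one.

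Both planned readings of the result are at stake. Equal scores would be taken as evidence that nothing of depth was lost, although content outside the podcast was not examined. A podcast deficit would be put down to missed nuance, although it would have arisen on points the podcast was expected to convey. No other outcome fills the gap: the secondary outcomes are self-reported motivation, cognitive load and perceived learning.

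**Working it through.** The plan gives no figure for podcast coverage, so there is nothing to reproduce. The sample-size figures do not bear on this point. The check has four steps.

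**1. What can lower a podcast score under the item rule**

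| Source of a podcast deficit | Visible in the score? |
|---|---|
| Article content that an accurate summary omits | Largely not: such items are excluded |
| Tested point unexpectedly missing or wrong in the actual podcast | Yes |
| Tested point mentioned, but with less detail or without the figure | Yes, in part |
| Tested point fully covered, but learned less well by listening | Yes |

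Only the first row is removed, but it is the row closest to the stated mechanism.

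**2. Illustrative size of what is removed.** Let *u* be the share of key article points absent from the podcast, *p* the proportion of items readers answer correctly, and *g* the proportion a listener gets right on an unheard point. With equal learning of covered points:

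gap on a 10-item whole-article test = 10 × *u* × (*p* − *g*)

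All three inputs are assumptions. The number of answer options is not stated, so *g* is taken as 0.20 to 0.25 (five or four options).

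- *u* = 0.20, *p* = 0.70, *g* = 0.25: 10 × 0.20 × 0.45 = 0.9 points
- *u* = 0.40, *p* = 0.70, *g* = 0.20: 10 × 0.40 × 0.50 = 2.0 points
- Wider range, low end (*u* = 0.10, *p* = 0.60, *g* = 0.25): 10 × 0.10 × 0.35 = 0.35 points
- Wider range, high end (*u* = 0.50, *p* = 0.80, *g* = 0.20): 10 × 0.50 × 0.60 = 3.0 points

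If every tested point is fully covered, the expected contribution from omission is 0. If one tested item in ten is in fact not covered, it is 10 × 0.10 × (0.70 − 0.25) = 0.45 to 10 × 0.10 × (0.70 − 0.20) = 0.50 points. How near the real tests are to 0 depends on a comparison of items with transcripts that is not reported.

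**3. Consequence for the interaction.** Suppose omission is 0.40 for the technical and 0.20 for the narrative article. With *p* = 0.70 for both, the part of the interaction due to omission is 2.0 − 1.0 = 1.0 point (*g* = 0.20) or 1.8 − 0.9 = 0.9 (*g* = 0.25). If readers score 0.60 on the technical and 0.80 on the narrative article, it is 1.6 − 1.2 = 0.4 or 1.4 − 1.1 = 0.3. This component drops out under the item rule; any interaction from poorer learning of covered points stays.

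**4. What the test can still detect.** For a within-person modality difference of 1 point with 60 participants (two-sided 5% test, 58 degrees of freedom), the SD of the difference is SD × √(2(1 − ρ)).

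- SD 2.0, ρ = 0.3: 2.0 × √1.4 = 2.37; noncentrality √60 / 2.37 = 3.27; power 0.90
- SD 1.5, ρ = 0.5: 1.5 × √1.0 = 1.50; noncentrality √60 / 1.50 = 5.16; power above 0.99

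SD and ρ are assumed. This concerns the modality contrast only, not the interaction.

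**The case against.** The strongest defence is that the rule is one of fairness and content validity: ask only about points a faithful summary should contain, so that listeners are not marked down for material they never received. The test is described as one of key information, and for that target the rule is defensible. Replacing items that have already been reviewed and tested would be a choice between targets, not the correction of an error. This stands.

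A reader might infer more: that the endpoint cannot detect any loss of detail, that omission contributes exactly 0 points, or that the interaction hypothesis is left without a mechanism. The documents do not support this. The words on accuracy in the item rule are conditional, so an actual podcast that drops or distorts a tested point still loses marks. A point may be covered more thinly than in the article. The Introduction also names sequential processing, fixed pace, lack of easy access to figures, and shallow processing, all of which could widen the gap for the technical article on shared content.

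The illustrated magnitude is also open to challenge. Nothing in the documents suggests that 20–40% of key points are missing. Limitations describes participants with a strong internal medicine background, so performance on unheard points may be above chance; the gap shrinks as *g* rises towards *p*.

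The defence does not rescue the planned conclusions. Limitations acknowledges that modality and completeness are mixed, and justifies comparing a summary with a full article as naturalistic. It does not tell the reader that item selection has taken most of the completeness difference out of the score.

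**Conclusion.** The point holds as a mismatch between endpoint and conclusions. By design the primary endpoint is largely, not wholly, insensitive to article content that the podcast omits. It remains a usable comparison of how well key points common to both formats are learned. Equal scores would not show preserved depth, and would speak to accuracy only on the points tested. A deficit would not by itself show missed nuance. This rests on the wording of the item rule and of the Discussion and needs no numerical assumption.

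The size is not known. The 0.9 to 2.0 points out of 10 (0.35 to 3.0 over wider inputs) is an illustration under assumed coverage, reader accuracy and guessing, and is not an estimate of bias in this trial.

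**What to change.** At submission (August 2025) no participant had been recruited. Before recruitment:

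1. Code each of the 20 items against the two existing transcripts as fully, partly or not covered. Report knowledge scores by that coding alongside the total.
2. Define the primary outcome as comprehension of key points that both formats are expected to convey.
3. Under Anticipated Findings, limit the statements on depth and on missed nuance to those points. The Abstract's conclusions need at most a matching qualification.
4. In Limitations, state that item selection largely removes informational scope from the score.

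The cost is one pass of coding and some rewording, with no extra participants or visits.

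Optionally, if the trial wishes to speak about omission, add a few prespecified items drawn from the full article regardless of podcast coverage, reported separately as a secondary outcome. That costs item writing and a repeat of the faculty review and internal testing, and adds a little to the session. The existing items need not be replaced.

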#### Motivation

To gauge participants’ motivation and engagement during the learning task, we will use items from the Intrinsic Motivation Inventory (IMI) [27], a well-established instrument for assessing subjective motivation in experimental tasks. We will focus on the interest and enjoyment as well as the effort and importance subscales of the IMI, as these are most relevant here. The interest and enjoyment scale serves as a measure of how enjoyable or engaging the student found the activity (considered a self-report proxy for intrinsic motivation), whereas effort and importance indicate how much effort they invested and how important they perceived doing well to be. Participants rate their agreement with the scales’ 7 (interest/enjoyment) and 6 (effort/importance) statements (eg, “I enjoyed doing this activity very much”; “I put a lot of effort into this”) on a 7-point Likert response from “strongly disagree” to “strongly agree.” The IMI has been used in educational studies and has shown good psychometric properties in various contexts (Cronbach α >0.80 in similar studies) [28], allowing the use of mean scores across all items of a scale as the final score.

